### Procedures (Template)

3.4

CRC patients will be evaluated by an oncologist, and after the initial evaluation, the patient with indication on using modified GGQL formula and fit the eligibility criteria of this RCT will be referred for specific evaluation by an oncologist with at least 3-year experience in the evaluation and prescription of modified GGQL formula. All the included participants would sign terms of free and informed consent.

The participants fitting the criteria of inclusion will be randomized to be divided into two groups: the treatment group (using modified GGQL formula plus basic antitumor therapy) and the control group (basic antitumor therapy).

The first evaluation should occur before treatment and then the participants will accept 12 weeks treatment in the treatment group or the control group. And they will be evaluated each three weeks after interventions.

### Randomization and blinding

3.5

The process of randomization will be carried out by stratified block randomization method with the block size setting as four and six, and the center was taken as the stratified factor. The participants will be divided into the treatment group and the control group randomly with a ratio of 1:1. We will use the ‘Proc plan’ of SAS9.3 statistical analysis software for generating the random scheme. The central randomization system for clinical research (provided by the Oncology Department of Shanxi Hospital of Traditional Chinese Medicine) will be used for randomization. When qualified patients are enrolled, the randomization personnel or clinical investigators in each center will log into the central randomization system through telephone or Internet to apply for the randomization number.

Because of no herbal medicine used in the control group, it will hardly to blind the doctors and patients involved in this RCT.

### Intervention

3.6

After specific evaluation by an oncologist, the participant will be divided into one of the two groups according to the randomization.

The treatment group: basic anti-tumor therapy combined with modified GGQL formula.

Basic anti-tumor therapies include:

1.mFOLFOX6 (Oxaliplatin 85 mg/m^2^ d1 + Leucovorin 400 mg/m^2^ d1 + Fluorouracil 400 mg/m^2^ d1 + Fluorouracil 2-2.4 g/m^2^ 46 h), the treatment period is 14 days; or2.FOLFIRI (Irinotecan + Leucovorin 400 mg/m^2^ d1 + Fluorouracil 400 mg/m^2^ d1 + Fluorouracil 2–2.4 g/m^2^ 46 h), the treatment period is 14 days; or3.XELOX (Oxaliplatin 85 mg/m^2^ d1 + Capecitabine 850–1000 mg/m^2^ bid d1-14), the treatment period is 21 days.

Modified GGQL formula is mixing and powdering by *Gegen*, *Huangqin*, *Huanglian*, *Muxiang*, *Chunpi*, *Donggua’er*, and *Paojiang*, which offered by Preparation Center of Shanxi Province Hospital of Traditional Chinese Medicine. The patients are planned to be used modified GGQL formula for 12 weeks.

The control group: basic anti-tumor therapy (the same as above).

All patients will be supervised by an experienced oncologist during this study.

### Primary outcome measures

3.7

1.Quality of life: measured by SF-36 at the baseline, week 6 of treatment, and week 12 of treatment;2.TCM symptom score: measured by the form of TCM symptom at the baseline, week 6 of treatment, and week 12 of treatment;3.Progression-free survival (PFS): measured by follow-ups;4.Overall survival (OS): measured by follow-ups.

### Secondary outcome measures

3.8

1.Performance status: measured by Karnofsky score at the baseline, week 6 of treatment, and week 12 of treatment;2.Size of tumor: measured at the baseline, week 6 of treatment, and week 12 of treatment;3.Tumor marker in the serum: measured at the baseline, week 6 of treatment, and week 12 of treatment;4.Tumor microenvironment: measured by vascular endothelial growth factor receptor (VEGFR) and Th1/Th2 in the serum at the baseline, week 6 of treatment, and week 12 of treatment;5.Immune status: measured by subset of the class of T-cells in the serum at the baseline, week 6 of treatment, and week 12 of treatment.

### Safety evaluation

3.9

All adverse events (AEs) during and after treatment of modified GGQL formula should be recorded detailedly. AEs are including but not limited to nausea, vomiting, changes in stool characteristics and defecation habits, palpitations, headache, dizziness, anorexia, insomnia.

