## Introduction

1

Colorectal cancer (CRC) is one of the malignant tumors that seriously threaten human health. According to the 2020 global epidemiological statistics on cancer published by the International Agency for Research on Cancer (IARC) of the World Health Organization, CRC has the second highest mortality rate and the third highest incidence rate of all malignancies with 935,200 deaths and 1,931,600 new cases worldwide. In China, there were about 560,000 new cases of CRC in 2020.^[1]^ The incidence of CRC is the fourth highest among males and the third among females.^[2]^

Patients with CRC have no obvious symptoms in the early stage, only atypical symptoms such as abdominal discomfort, fecal occult blood or indigestion, which are not easy to attract patients’ attention. Once CRC diagnosed, 20% to 30% of patients are already in advanced stage, losing the chance of surgery.^[3]^ The 5-year survival rate for advanced CRC is <10%.^[4]^

Currently, the principle of treatment for early stage CRC is a multidisciplinary and comprehensive treatment based on surgery. While 50% of patients with CRC may have recurrence or metastasis within two years after radical surgery, of which 20% to 30% have local recurrence and 50% to 80% have distant metastasis.^[5]^

For patients who cannot be resected, chemotherapy is recommended.^[6]^ However, chemotherapy drugs often show significant toxic side effects, such as reduction of autoimmunity, inhibition of bone marrow hematopoiesis and gastrointestinal reactions. Therefore, therapies which can increase efficacy and reduce side effects of chemotherapy need to be developed.

Chinese herbal medicine (CHM) has advantages in the treatment of tumors, with the effect on improving clinical symptoms, enhancing patients’ immunity and quality of life, reducing the adverse effects of radiotherapy and chemotherapy, and prolonging survival through the coordinated effects of multiple components, targets and pathways in the process of tumor occurrence and development.^[7]^

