## Objective

2

In this study, we will evaluate the clinical efficacy and safety of modified GGQL formula for patients with advanced CRC with the type of damp-heat. We will also aim to investigate the relationship between modified GGQL formula and life quality of CRC patients and cellular immunity.

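### As written, adverse event recording follows exposure to the formula, which control patients never have, so safety cannot be compared between the arms

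*Protocol article*

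**What the plan says.** Section 2 (Objective) makes safety part of the trial's question: "we will evaluate the clinical efficacy and safety of modified GGQL formula for patients with advanced CRC with the type of damp-heat".

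Section 3.9 (Safety evaluation) gives the recording rule: "All adverse events (AEs) during and after treatment of modified GGQL formula should be recorded detailedly". It adds an open list of examples: "AEs are including but not limited to nausea, vomiting, changes in stool characteristics and defecation habits, palpitations, headache, dizziness, anorexia, insomnia".

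Section 3.6 gives both arms the same choice of chemotherapy regimens and adds the formula in the treatment arm only. Section 3.5 gives the lack of blinding its reason: "Because of no herbal medicine used in the control group". There is no placebo.

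Section 3.4 has participants of both groups evaluated every three weeks, and section 3.6 places all patients under an oncologist's supervision. Neither section mentions AEs. AEs are not among the outcomes in sections 3.7 and 3.8, and section 3.12 does not refer to them.

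**The concern.** A recording rule anchored on the experimental product works in a single-arm study. In a randomised trial against chemotherapy alone, it defines a window that only one arm can enter. Site staff who follow section 3.9 to the letter would complete AE records for treatment-arm patients and would have no instruction for control patients.

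The shared background treatment makes this matter. The Introduction describes chemotherapy's harms as "reduction of autoimmunity, inhibition of bone marrow hematopoiesis and gastrointestinal reactions". If nausea or a change in stool habit is recorded in the treatment arm, only the rate of the same event under chemotherapy alone can show whether the formula added to it, reduced it or left it unchanged. The Introduction also argues that "therapies which can increase efficacy and reduce side effects of chemotherapy need to be developed", and a reader will expect AE data from this trial to bear on that.

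The trial is open label, so the remedy has to cover the method of recording as well as the window. If control-arm events were noted informally while treatment-arm events were sought under a rule, the comparison would be biased by unequal questioning.

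**Working it through.** The article states no figure on this point, so the check is mainly a reading of the sections against one another. A short calculation then shows what a two-arm comparison could deliver.

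**Step 1: whom the rule reaches.**

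| Element | Treatment arm | Control arm | Source |
|---|---|---|---|
| Chemotherapy | yes | yes, same regimens | 3.6 |
| Modified GGQL formula | yes, 12 weeks | none | 3.5, 3.6 |
| A period during or after formula treatment | exists | does not exist | follows from the row above |
| AE recording under 3.9 | required | not provided for | 3.9 |
| Three-weekly evaluation | yes | yes, AEs not mentioned | 3.4 |
| Oncologist supervision | yes | yes, AEs not mentioned | 3.6 |

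**Step 2: whether another section fills the gap.** Sections 3.7 and 3.8 (outcomes), 3.11 (baseline data) and 3.12 (analysis) contain no AE rule. Section 3.9 stands alone.

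**Step 3: whether treatment-arm AEs could be interpreted alone.** Nausea, vomiting, anorexia and stool changes in the section 3.9 list are gastrointestinal complaints, and the Introduction attributes gastrointestinal reactions to chemotherapy. A treatment-arm rate is therefore a sum of chemotherapy and formula effects. Without the control-arm rate the two parts cannot be told apart.

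**Step 4: precision if both arms were recorded.** Inputs: 120 patients and 20% drop-out (section 3.10), and 1:1 allocation (section 3.5). This gives 120/2 = 60 per arm, or 60 × 0.8 = 48 per arm after drop-out. The article gives no AE rate, so a range of rates p, common to both arms, is assumed. The 95% half-width for a difference in proportions is 1.96 × √(2p(1−p)/n).

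| Assumed p | n = 60 per arm | n = 48 per arm |
|---|---|---|
| 10% | 1.96 × √(0.18/60) = 0.107 | 1.96 × √(0.18/48) = 0.120 |
| 30% | 1.96 × √(0.42/60) = 0.164 | 1.96 × √(0.42/48) = 0.183 |
| 50% | 1.96 × √(0.50/60) = 0.179 | 1.96 × √(0.50/48) = 0.200 |

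These half-widths describe what the corrected rule would allow. They do not measure the defect, which is that no between-arm estimate is provided for.

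**The case against.** The strongest reply is that one loosely worded sentence in a condensed article is being read too literally. Section 3.9 sets a duty for the formula arm and does not forbid recording in controls. Both groups are seen every three weeks, and control-arm events may well be noted then. Section 3.3.3 has a similar slip: it defines withdrawal by unwillingness to use the formula, which does not fit control patients either. AE forms, grading and tables normally sit in the full protocol.

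Part of this stands. That recording happens in the treatment arm only is an inference from section 3.9 being the sole rule; the article does not say it. Grading scales and laboratory schedules are detail that an article may leave out, and their absence is not held against it here. The window is different: the article does state one, and it leaves out half of the randomised patients.

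A reader might also infer three stronger points that the document does not support:

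- **That bone marrow suppression is left out of AE recording.** The rule covers all AEs, and the named events are explicitly examples. Nothing is omitted by not being named.
- **That the safety objective cannot be addressed at all.** AEs in the formula arm, including serious or unexpected ones, can still be described. Only the comparative answer is lost.
- **That the idea of better-tolerated chemotherapy goes wholly untested.** This is background motivation. It is not a listed objective or outcome. SF-36, TCM symptom score, Karnofsky score and T-cell subsets are planned at baseline, week 6 and week 12 without restriction to one arm, and they capture part of tolerability. They do not replace AE rates.

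**Conclusion.** The point holds as a defect of wording with a real consequence. Followed as written, section 3.9 yields AE data for the arm that takes the formula and makes no provision for the other. The safety objective in section 2 could then be met descriptively but not comparatively, and gastrointestinal events in the treatment arm could not be separated from chemotherapy toxicity.

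A two-arm comparison would have a 95% half-width of about 18 points with 60 per arm, or about 20 points with 48 per arm, at an assumed 50% AE rate. At an assumed 10% rate it would be about 11 or 12 points. That precision is modest: it could show large differences in common events and little else. The figures rest on an assumed rate common to both arms and on drop-out falling equally.

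The conclusion itself rests on the wording of section 3.9 and on the absence of any other AE rule in the article. A full protocol that already requires the same recording in both arms would reduce this to a correction of the article's text.

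**What to change.** Reword section 3.9 so that AEs are recorded in all randomised patients in both arms, starting at randomisation, over a window of the same length, at the same three-weekly visits and by the same method. State that AE proportions will be compared by arm, with 95% confidence intervals for the differences. The end of the window should be counted from randomisation, not from the last dose of the formula, so that it applies equally to controls.

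The change takes a sentence or two and a common AE form. Section 3.4 already has both groups evaluated every three weeks, so no visits are added. The downside is a little more data entry for control patients. It should be in place before the first patient is enrolled, because AEs that were not sought systematically cannot be reliably recovered later.

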### Sample size calculation

3.10

The number of participants is capable to detecting according to the results of the previous study (1-year survival rate was 80% and the median overall survival was 25 months in the treatment group; 75% and 22 months respectively in the control group) with an alpha error of 0.05 and beta error of 0.2. Considering the 20% drop-out rates, the sample will be composed of 120 participants randomized into two groups.

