### Statistical analysis

3.12

The analysis will follow the principle of intention to treat (ITT). All statistical tests were conducted by two-sided tests and P values less than 0.05 were considered statistically significant. The description of quantitative indicators will calculate the number of cases, mean, standard deviation, median, minimum and maximum. Classification indicators are described by the number of cases and percentages of each category. For quantitative data, a mixed effect model was used to compare the change values of the two groups before and after treatment. The baseline score was taken as a covariable, and the grouping and central effect were considered in this analysis model. The dependent variable is the base change value of comparison point at each time point after treatment. Based on this model, the least square mean (LSMEAN) and the 95% confidence interval of the two groups will be calculated respectively. Kaplan–Meier method will be used to draw OS and PFS survival curves, and log-rank will be used to test the differences between the two groups. The differences of OS and PFS will be discussed in subgroup analysis according to age, sex, left and right colon, gene status, and microsatellite status.

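### The stated 80% power does not follow from the survival figures in section 3.10: 120 patients give roughly 5–11% power for overall survival on the quoted figures, and at most about 28% on the most favourable reading

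*Protocol article*

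**What the plan says.** Section 3.10 of the protocol article takes its inputs from a previous study: "1-year survival rate was 80% and the median overall survival was 25 months in the treatment group; 75% and 22 months respectively", where the second pair of figures belongs to the controls. It says that the trial can detect this difference "with an alpha error of 0.05 and beta error of 0.2". The total follows: "Considering the 20% drop-out rates, the sample will be composed of 120 participants randomized into two groups".

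Other sections supply the rest:

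- Section 3.5 allocates patients 1:1.
- Section 3.7 lists four primary outcomes: SF-36 quality of life, TCM symptom score, progression-free survival (PFS) and overall survival (OS).
- Section 3.12 compares OS by the log-rank test and fixes the level: "All statistical tests were conducted by two-sided tests and P values less than 0.05 were considered statistically significant".
- Section 3.1 gives a trial duration of 2 years. Section 4.1 has recruitment running from 1 October 2021 to 30 September 2023, which fills the same 24 months.

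The article gives no formula, hazard ratio, target number of deaths or length of survival follow-up.

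**The concern.** A gain of 5 percentage points in one-year survival, or of 3 months on a 22-month median, is a small effect. Trials that detect such effects need patients or deaths in the thousands, not 96 evaluable patients. The section therefore joins an effect, an error rate and a sample size that do not appear to fit together. This is a matter of what is stated, not of missing detail: a fuller protocol or an analysis plan could add to the published combination but could not make it correct.

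OS is a primary outcome. If power is far below the stated 80%, a non-significant log-rank test carries very little information about the planned benefit, and a reader relying on beta 0.2 would give it too much weight. A significant result would need an observed effect far larger than the planned one. The calculation is also the only justification given for the size of the trial.

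**Working it through.** **Inputs.** From section 3.10: one-year survival 80% versus 75%, median OS 25 versus 22 months, alpha 0.05, power 0.80, drop-out 20%, N = 120. From section 3.12: two-sided tests, log-rank for OS. From section 3.5: 1:1 allocation. Normal quantiles: 1.960 and 0.8416, sum 2.8016.

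**Reproducing the plan's figure.** The drop-out step fits: 96 / 0.8 = 120, or 48 evaluable per arm. The 96 itself could not be reproduced from the survival inputs by any of the variants below.

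**One-year survival, two proportions.** n per arm = [1.960·√(2·0.775·0.225) + 0.8416·√(0.80·0.20 + 0.75·0.25)]² / 0.05² = (1.1575 + 0.4961)² / 0.0025 ≈ 1,094. That is 2,188 evaluable in total, and 2,188 / 0.8 = 2,735 with drop-out. A one-sided test still needs 1,724 before drop-out; a continuity correction raises the two-sided total to 2,268.

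Power with 48 per arm: Φ[(0.05 − 1.960·√(0.34875/48)) / √(0.3475/48)] = Φ(−1.376) = 8.4%. With 60 per arm: Φ(−1.306) = 9.6%.

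**Log-rank test, hazard ratio from the medians.** Under constant hazards HR = 22/25 = 0.88. Deaths needed (Schoenfeld) = 4·2.8016² / (ln 0.88)² ≈ 1,922, which is 16 times the 120 patients enrolled. Freedman's formula gives 1,927. One-sided, the figures are 1,514 and 1,518.

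**Log-rank test, most favourable reading.** If the one-year rates are turned into a hazard ratio that holds throughout, HR = ln 0.80 / ln 0.75 = 0.776. Deaths needed: 487 (Schoenfeld) or 492 (Freedman); one-sided, 384 or 388.

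**Power by number of deaths.** Two-sided power = Φ(√(D/4)·|ln HR| − 1.960). Follow-up after accrual is not stated, so it is varied as an assumption. Expected deaths D use exponential survival with the quoted medians and uniform accrual over 24 months. Each cell shows 96, then 120 patients.

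| Follow-up after accrual (assumed) | Deaths D | Power at HR 0.88 | Power at HR 0.776 |
|---|---|---|---|
| 0 months | 27 / 34 | 5.2% / 5.6% | 9.7% / 11.2% |
| 12 months | 48 / 60 | 6.4% / 7.1% | 14.0% / 16.4% |
| 24 months | 62 / 78 | 7.3% / 8.1% | 16.9% / 20.0% |
| 36 months | 72 / 90 | 7.8% / 8.8% | 18.9% / 22.6% |
| Every patient dies | 96 / 120 | 9.1% / 10.4% | 23.7% / 28.5% |

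Adding rejections in the wrong direction moves the HR 0.88 column to 6.3% at the bottom and 10.8% at the top, hence the overall range of about 5–11%.

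**What 96 could detect.** With 96 deaths, 80% power needs HR = exp(−2.8016/√24) ≈ 0.56. For a continuous week-12 score with 48 per arm, the detectable standardised difference is 2.8016·√(2/48) ≈ 0.57 at two-sided 0.05. At two-sided 0.0125 (quantile 2.498) it is 3.339·√(2/48) ≈ 0.68.

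**The case against.** The strongest objection is that there is no single actual power. The article states neither follow-up nor a death count, and HR 0.88 assumes constant hazards, which the quoted figures contradict: a constant hazard with a 22-month median gives 68.5% alive at one year, not 75%, and a 25-month median gives 71.7%, not 80%. The figures suggest a rising hazard, under which the effect on the hazard scale may be larger than 0.88 implies. This stands, and it is why ranges are given and the HR 0.776 reading is included. It does not rescue the claim, because the top of that reading, with all 120 patients dead, is still about 28%. A one-sided test would raise that to 40%, but section 3.12 specifies two-sided tests.

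Four stronger readings are tempting, and the document does not support them:

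- A reader might infer that the medians and the one-year rates contradict each other under proportional hazards. They conflict only under constant hazards. Both fit HR 0.776 if control survival at 25 months is 0.5^(1/0.776) = 0.41, a steep fall from 0.50 at 22 months but a possible one.
- A reader might infer that PFS is equally underpowered. The article gives no PFS median, rate or hazard ratio, so its power cannot be computed.
- A reader might infer that the investigators will report a null OS result as showing no benefit. The article does not say how such a result will be interpreted; the risk follows only from the stated beta.
- A reader might conclude that OS and PFS should lose their primary status or their tests. The arithmetic does not require that.

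**Conclusion.** The point holds. The stated effect, error rates and sample size cannot all be true together, and the gap is more than tenfold, so it is neither rounding nor choice of formula. Either quoted input is enough alone: about 1,094 evaluable patients per arm for the one-year rates, or about 1,922 deaths for the medians under constant hazards.

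Two-sided power for OS is about 8–10% on the one-year comparison (48 to 60 per arm) and about 5–11% on the log-rank test at HR 0.88 (27 to 120 deaths). It is about 10–28% if HR 0.776 is applied throughout. The position within these ranges depends on follow-up and on the shape of the hazard, which the article does not fix. The conclusion that power is far below 80% depends on neither.

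Three of the four primary outcomes (SF-36, TCM symptom score and PFS) do not enter the calculation, so section 3.10 offers no other basis for 120. This must be corrected, because it is the sole stated justification of the trial's size.

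**What to change.** Keep 120 patients and change the text:

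1. In section 3.10, delete the claim of beta 0.2 for 80% versus 75% one-year survival and for 25 versus 22 months.
2. State the actual OS power together with the follow-up and number of deaths assumed: about 5–11% on the quoted figures, and at most about 28% on the most favourable reading.
3. Present the OS result with its hazard ratio and confidence interval beside the log-rank test, so that a non-significant test is not taken as evidence against the planned benefit.
4. If the size is to rest on a week-12 score instead, say so and name the score. Note that 48 evaluable per arm gives 80% power only for a standardised difference of about 0.57 at two-sided 0.05, or about 0.68 at 0.0125 if alpha is divided over four primary outcomes. These values are worked back from the sample size, and no standard deviation or minimal important difference in the article supports them. The sponsor would have to justify that such a difference is plausible.

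The cost is a rewritten section 3.10 and a sentence on how OS is reported, with no extra patients. The downside is that the stated power becomes much less favourable.
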